#### Random assignment

Randomization of eligible participants will occur within one week after screening. A randomization module has been created on REDCap, using a 1:1 permuted block design. Study assignment is unblinded. Participants and medical staff will be notified of the study arm assignment. It is anticipated that screening, the consent process, randomization, and treatment induction will likely occur within a 5-day window. While randomization to the experimental condition will not guarantee XRB induction, every practical effort will be made to induct participants onto XRB prior to release. It is, however, the nature of the unsentenced population that release dates are unpredictable. The percentage of participants in the experimental condition who do initiate XRB prior to release will be an important implementation finding of this project.

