##### SLB

As described above, participants will already be receiving SLB and be participating in the MATADOR program. If randomized to the SLB arm, they will continue treatment as usual in the facility.

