We will use a modified intention-to-treat (mITT) approach. The primary analysis sample will be participants randomized and released to the community. Clinical trials in the criminal legal system usually see a small rate of randomized participants initially planning for release, then sentenced, transferred, or otherwise incarcerated for longer periods of time due to unanticipated post-randomization factors independent of the study. This effectively renders the now randomized participant ineligible, as they are unable to leave the jail and continue treatment in the community. Thus, participants not released to the community as planned will be excluded from the analysis of the primary outcome. Participants who are not released to the community do not enter the risk set for outcomes that can only be observed at release or in the community after release. While we do not expect arm differences in the probability of release to the community, we will examine this as an exploratory outcome descriptively and with a Fisher’s exact test in intent-to-treat (ITT) analysis. In other ITT analyses, the approach will be outcome-dependent. For the outcomes of buprenorphine in a participant’s system at release and participation in MOUD treatment following release, these participants would be coded as No. For buprenorphine diversion during incarceration, these cases need no special treatment since the outcome does not depend on release. For rearrests, ITT analysis would code these participants as not rearrested. In all modified intent-to-treat (mITT) or per protocol analysis of outcomes observed at or after release to the community, participants not released to the community will be excluded. We expect this to occur among fewer than 5% of all participants who are randomized. Secondary analyses will examine all randomized participants (ITT) and participants both inducted and released as planned (per protocol). Sensitivity analyses will examine the effect of competing risks (i.e. incarceration or death) after release on the primary outcomes.

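### The secondary per-protocol set applies an induction condition that in practice binds only in the XRB arm, so it selects one arm on length of stay and willingness to be injected

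*Protocol article*

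**What the plan says.** The Planned analyses section names three analysis sets. The primary one is mITT: "The primary analysis sample will be participants randomized and released to the community". Secondary analyses use all randomised participants (ITT) and "participants both inducted and released as planned (per protocol". One wording of the per-protocol set serves both arms, and no SLB equivalent of induction is given.

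The Random assignment section treats induction as uncertain in the XRB arm: "While randomization to the experimental condition will not guarantee XRB induction, every practical effort will be made to induct participants onto XRB prior to release". The reason it gives is "the nature of the unsentenced population that release dates are unpredictable". It adds: "The percentage of participants in the experimental condition who do initiate XRB prior to release will be an important implementation finding of this project". Under XRB induction, the step is a sublingual dose followed by the injection an hour later if there is no precipitated withdrawal.

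The SLB section has no such step: "participants will already be receiving SLB and be participating in the MATADOR program". It continues: "If randomized to the SLB arm, they will continue treatment as usual in the facility". The SLB test dose in the inclusion criteria is passed before randomisation, whichever arm is then assigned.

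**The concern.** A per-protocol set should ask the same kind of thing of each arm. Here an XRB participant qualifies only by remaining in custody until the injection and accepting it, while an SLB participant qualifies on induction almost automatically. The documented cause of failed induction is unexpected release, so the XRB side loses its shortest stays and the SLB side keeps them. People released without notice are also the group that the Introduction gives as the reason for early induction.

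The result could be read as the effect of XRB in those who received it. For release with active buprenorphine, it would mix that effect with the removal of XRB participants who may have had poor results. For the 90-day outcomes, it would mix it with differences in length of stay and readiness for treatment.

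**Working it through.** **1. The plan's own figures.** The XRB rate is 0.75 and the risk ratio 1.34, so the implied SLB rate is 0.75 / 1.34 = 0.560. The odds ratio is (0.75/0.25) / (0.560/0.440) = 2.36, which rounds to the stated 2.4. With 100 per arm and two-sided alpha 0.05 (assumed; the article does not state it), power is 0.813, and 97 per arm are needed for 0.80. The stated power reproduces and is not in dispute. The same section also calls the outcome rare under SLB, which does not fit 0.560; I use 0.560 because the stated power rests on it.

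**2. How many XRB participants might the condition remove?** The article gives no induction share. As an assumption, take exponential stays with the 32-day mean quoted in the Introduction, and an injection at day 5 (the expected window in Random assignment) or day 7 (the week-long induction phase in the Discussion).
- Released before day 5: 1 − exp(−5/32) = 14%. Before day 7: 1 − exp(−7/32) = 20%.
- Among stays longer than 4 days: 1 − exp(−1/32) = 3%, and 1 − exp(−3/32) = 9%.
- Mean stay of those inducted: about 37 to 39 days, against 32 overall.

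Early release alone could thus remove about 3% to 20% of the XRB arm. Refusal, precipitated withdrawal or a clinical decision would add to this. I use f = 0.80 to 0.95.

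**3. Effect on the risk ratio.** Let f be the share of released XRB participants who were inducted and u the outcome rate in those who were not.

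Rate in the inducted = (overall XRB rate − (1 − f) × u) / f. Per-protocol RR = that rate / 0.560.

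*No true arm difference (overall XRB rate 0.560).* Example: f = 0.80, u = 0.20 gives (0.560 − 0.04) / 0.80 = 0.650, so RR = 1.16.

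| f | u = 0.20 | u = 0.40 | u = 0.56 |
|---|---|---|---|
| 0.95 | 1.03 | 1.02 | 1.00 |
| 0.90 | 1.07 | 1.03 | 1.00 |
| 0.80 | 1.16 | 1.07 | 1.00 |

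*Design effect (overall XRB rate 0.75, RR 1.34).* Example: f = 0.80, u = 0 gives 0.75 / 0.80 = 0.9375, so RR = 1.68.

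| f | u = 0 | u = 0.20 | u = 0.40 |
|---|---|---|---|
| 0.95 | 1.41 | 1.39 | 1.37 |
| 0.90 | 1.49 | 1.45 | 1.41 |
| 0.80 | 1.68 | 1.59 | 1.50 |

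**4. How much of that is selection?** Some rise above 1.34 is legitimate, because an effect confined to those inducted is diluted in the whole arm. If assignment alone does nothing in those not inducted, and no SLB participant receives XRB, the effect in the inducted is (0.75 − 0.560) / f. The per-protocol risk difference exceeds it by (1 − f) × (0.560 − u) / f.
- f = 0.80, u = 0.20: per protocol 0.8875 − 0.560 = 0.328; complier 0.190 / 0.80 = 0.238; excess 0.25 × 0.36 = 0.09.
- f = 0.95, u = 0.40: per protocol 0.768 − 0.560 = 0.21; complier 0.190 / 0.95 = 0.20; excess under 0.01.

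The excess is zero at u = 0.56 and favours XRB whenever u is lower. It would change sign if those not inducted did better than the SLB arm.

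**The case against.** The strongest points on the other side are these.

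- *The set is secondary.* This stands. The mITT and ITT analyses carry no induction condition, and the share inducted will be reported, so the loss will be visible. It limits the importance of the point but does not make the comparison valid.
- *The analysis plan may define an SLB counterpart.* The Participant withdrawal section already speaks of initiating or continuing the treatment relevant to the arm. But continuing SLB is met at once and starting XRB is not, so early releases would still be lost from one arm only. The stated criterion needs replacing, not elaborating.
- *The loss may be small.* This partly stands. Anticipated stays under 4 days are excluded and induction is expected quickly; the lower end of step 2 is 3%. The exclusion concerns anticipated stay, however, and actual release is unpredictable.
- *Induction is not strictly an XRB-only matter.* Participants who enter through the test dose may still need SLB set up. So the condition binds almost only, not absolutely only, in the XRB arm.

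A reader might infer that the XRB rate in this set is close to 100% by construction, because injection within 28 days of release counts as success. The documents do not support that. Custody can last up to 6 months within the study, and XRB maintenance allows a missed dose to be given up to 8 weeks after the prior one, so an inducted participant can be outside 28 days at release.

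A reader might also take 1.00 / 0.56 = 1.79 as the likely risk ratio. That is only the ceiling, at f = 0.75 and u = 0. It reuses the assumed outcome rate of 75% as an induction rate and supposes that nobody left on SLB succeeds, although SLB in the past 24 hours also counts.

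**Conclusion.** The point holds for the secondary per-protocol comparison. As worded, the set conditions one arm on an event after randomisation that is linked to length of stay and acceptance of treatment, and leaves the other arm nearly intact. The bias tends to favour XRB. For f of 0.80 to 0.95, the per-protocol risk ratio is about 1.00 to 1.16 with no true effect (u of 0.20 to 0.56) and about 1.37 to 1.68 under the design effect (u of 0 to 0.40). Part of the latter rise is removal of dilution, not bias.

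These sizes are illustrative: f and u are assumptions, and the SLB rate is the one implied by the stated risk ratio. The documents do not support saying that the result will be strongly positive whatever XRB does; with no true effect, the distortion over this range is nil to moderate. The primary conclusion of the trial is not at risk. The change is worth making because it is cheap and the replacement is less biased.

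**What to change.** Replace the per-protocol comparison with a complier-average effect among released participants, using randomisation as the instrument: the risk difference between arms divided by the difference between arms in the proportion who received XRB. State the assumption that assignment alone has no effect in those not inducted; in an unblinded trial this deserves a sentence of justification. If the rate among inducted XRB participants is still reported, label it descriptive and not a comparison with SLB.

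If a landmark sensitivity analysis is added, count it from randomisation and apply it identically to both arms, whether or not the participant was injected. The 5-day window in Random assignment does not serve as it stands, because it starts at screening and is only an expectation.

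The cost is a change of wording in the protocol and analysis plan and a few lines of code, with no new data collection. The interval is wider. With f = 0.80, u = 0.20, 100 released per arm and f treated as known, the half-width for the complier risk difference is 1.96 × √(0.75×0.25/100 + 0.56×0.44/100) / 0.80 = 0.16. The per-protocol half-width is 1.96 × √(0.8875×0.1125/80 + 0.56×0.44/100) = 0.12.

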## Discussion/conclusions

Given the high prevalence of opioid use among adults involved with the criminal legal system in the United States, it is critical to identify and treat jail residents who meet the criteria for OUD. Although most jail-based studies have focused on initiating MOUD for sentenced residents nearing release, this study targets pre-trial residents. Those under pre-trial status are generally more difficult to treat with XRB, as their uncertain discharge dates reduce providers’ confidence in completing the weeklong induction phase. But successfully initiating XRB for this population is likely to increase the rate of participants leaving jail with a clinically active dose of buprenorphine in their system and reduce their risk of opioid-related relapse and overdose during the high-risk phase immediately following release from jail. Findings from this study will demonstrate the feasibility and outcomes of inducting pre-trial adults with OUD onto XRB, as well as offer practical clinical and policy guidelines on how best to do so. Final outcomes are expected by spring of 2027.

## Data Availability

No datasets were generated or analysed during the current study.
